## Abstract

**Background:**

Smoking is a leading cause of preventable death, disproportionately affecting people with low socioeconomic status (SES) and serious psychological distress (SPD). The U.S. Food and Drug Administration (FDA) has proposed reducing nicotine levels in cigarettes and other combusted tobacco products to minimally addictive levels, a policy with significant public health potential. However, misperceptions about very low nicotine cigarettes (VLNCs), such as beliefs that they are less harmful or ineffective for quitting, may reduce policy effectiveness. While previous randomized controlled trials (RCTs) have examined the effects of using VLNCs, none have incorporated messaging to address misperceptions. This study evaluates the impact of a messaging campaign on smoking behaviors, risk perceptions, and quit intentions among people who smoke, focusing on individuals with low SES, SPD, and neither. The primary objective is to assess whether exposure to VLNC-related messages reduces the number of cigarettes smoked per day compared to VLNC use alone. Secondary objectives include examining effects on other tobacco product use, nicotine dependence, forgoing cigarettes, perceived risks, and quit intentions.

**Methods:**

This multi-site, open-label, parallel-arm RCT will enroll 1230 adults who smoke (*n* = 410 per group: with SPD, low SES, neither category). After a 1-week baseline period, participants will be randomized (1:1) to receive either (1) VLNCs with messaging or (2) VLNCs only (control). Messaging will include pack inserts and digital ads shown during weekly visits to address misperceptions and encourage quitting. Participants will complete daily logs via text messages and attend weekly visits over 4 weeks for data collection, including self-reported smoking behavior, expired carbon monoxide (CO) samples, and questionnaire assessments. The primary outcome is the number of cigarettes smoked per day in the final study week (week 4). Secondary outcomes include the use of other tobacco products, nicotine dependence, forgoing cigarettes, and quit intentions.

**Discussion:**

This trial will be the first to examine the effects of a messaging campaign accompanying VLNC use among priority populations. Results will inform FDA regulatory strategies and public health messaging to support nicotine reduction policy implementation.

**Trial registration:**

ClinicalTrials.gov NCT06787937. Registered on 22 January 2025.

## Administrative information {1b}

**Table Taba:** 

Item	Description
Primary Registry and Trial Identifying Number {4}	ClinicalTrials.gov, NCT06787937. Registered 22 January 2025. (URL: https://clinicaltrials.gov/study/NCT06787937?term=NCT06787937&rank=1)
Secondary Identifying Numbers	n/a The trial is registered only at ClinicalTrials.gov; no additional registry numbers.
Source(s) of Monetary or Material Support	Research reported in this publication was supported by the National Cancer Institute of the National Institutes of Health and the Food and Drug Administration Center for Tobacco Products (R01CA239308).
Primary Sponsor and contact information {3b}	Georgia State University. [name]
Role of sponsor and funder {3c}	The content is solely the responsibility of the authors and does not necessarily represent the official views of the National Institutes of Health or the Food and Drug Administration. The funders had no role in study design, data collection and analysis, decision to publish, or preparation of the manuscript.
Contact for Public Queries	[name], Telephone: [name]; E-mail:[contact]
Contact for Scientific Queries	[name], Telephone: [name]; E-mail:[contact]
Public Title	Nicotine intervention and communication for empowering reduction among priority populations of people who smoke (the NICER study)
Scientific title	The NICER Study (Nicotine Intervention and Communication for Empowering Reduction) protocol: a randomized controlled trial evaluating effects of messages about reduced nicotine cigarettes and policy
Countries of Recruitment	United States
Health Condition(s) or Problem(s) Studied	Smoking
Intervention(s)	Message campaign
Key Inclusion and Exclusion Criteria	Inclusion criteria: Adults aged ≥ 21 years who self-report having smoked ≥ 100 cigarettes in their lifetime and currently smoke on ≥ 27 of the past 30 days; expired breath carbon monoxide (CO) ≥ 6 ppm confirming regular smoking; able to speak, read, and write in English; available for the study period; and willing to use the study cigarettes. Exclusion criteria: Current pregnancy or lactation, or intent to become pregnant within the next 2 months; living in the same household as an enrolled participant; or unwillingness to use the study cigarettes as part of the trial.
Study Type	This is a multi-site, parallel-group, open-label randomized controlled trial with a 1:1 allocation to the treatment condition and control condition.
Date of First Enrollment	First enrollment began 11 September 2025
Sample Size	1,230
Primary outcome(s)	Cigarettes smoked per day
Key Secondary outcome(s)	Use of other tobacco products; Use of nicotine replacement therapy; Perceived risks of smoking VLNCs; Quit intention; Nicotine dependence; Forgoing cigarette behaviors.
Ethics Review	This study was approved by the GSU institutional review board (protocol H25318).
Individual Trial Participant Data sharing statement	All study data will be deposited in the ScholarWorks@Georgia State University institutional repository within 1 year of study completion. The compiled dataset will be publicly accessible through the ScholarWorks@Georgia State University website. Users seeking access must adhere to specific conditions as specified by the ScholarWorks. Redistribution of the data to third parties will not be permitted.

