### Objectives {10}

The primary objective of the study is to examine the effect of messages about VLNCs accompanied by VLNC use (vs. use of VLNCs without messages) on the number of cigarettes smoked per day among people who smoke from three groups: those with past-month serious psychological distress (SPD), those with low SES, and those in neither category. The secondary objectives are (1) to examine the effect of messages about VLNCs in combination with VLNC use (vs. use of VLNCs without messages) on the use of other tobacco products (e.g., cigarillos, e-cigarettes), cigarette dependence, and cessation-related outcomes over the study period, and (2) to examine the effect of messages about VLNCs in combination with VLNC use (vs. use of VLNCs without messages) on perceptions and behavioral intentions.

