### Criteria for discontinuing or modifying allocated intervention/comparator {15b}

At each weekly visit, participants will be asked if they have made a quit attempt in the past week.

If a participant has made a quit attempt in the past week, research staff will:Encourage the participant to continue abstaining from smoking.Schedule normal weekly visits.Provide the participant with the tobacco quitline number.Offer the option to either take home the study product or decline it. If the participant chooses to take home the study product, recommend they store the product out of sight to avoid smoking triggers.

If the participant declines the study product, instruct them to contact the research coordinator if they lapse and would like to pick up the product before the next visit.

For the safety concerns, participants will be withdrawn immediately from the study if any of the following occur:Cardiovascular disease (CVD) event: Typically includes MI (heart attack), PTCA (angioplasty/stenting), bypass surgery, stroke, peripheral vascular disease (arterial blockages in arms or legs leading to procedure or surgery). Less common CVD problems would be new cardiac arrhythmias (e.g., new atrial fibrillation) or new valvular disease (e.g., mitral or aortic regurgitation).DVT/PE (deep vein thrombosis/pulmonary embolism, i.e., blood clots in the venous system).Psychiatric Hospitalization: A subject will be withdrawn if they are hospitalized for psychiatric reasons at any time during participation in the study.Pregnancy: If subject indicates they are pregnant or have a positive pregnancy test after receipt of study products, they will be withdrawn from the study if they are continuing to use any tobacco product, and the pregnancy will be documented as an adverse event that will remain open until delivery. At that time the research staff will contact the participant to ask a few questions about the baby’s health and will update the open Adverse Event.Expired breath CO increase: A subject will be withdrawn from the study if the average of the 2 CO readings is 100 ppm or greater.

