### Secondary outcomes

The following outcomes will be based on 7 days’ daily logs submitted through text message prompted surveys during the last week of the trial (before the week 4 visit). Use of other combusted (e.g., little cigar and cigarillos) and noncombusted (e.g., e-cigarettes) products will be assessed by asking participants to enter an integer indicating the number of each product used per day. Use of nicotine replacement therapy (NRT) or prescription cessation medications will be assessed using a multiple-choice question, allowing participants to select all NRT or prescription cessation medications used from a provided list of options.

The following outcomes will be based on a questionnaire completed during the week 4 visit. Perceived risks of smoking VLNCs will be measured by asking participants’ perceived likelihood of overall harm to health under conditions of smoking VLNCs [33]. Response options range from 1 (Not at all likely) to 5 (Extremely likely), with higher scores representing a better outcome. An additional option, “Don’t know,” is also provided. Self-efficacy to quit smoking will be measured with multiple items, assessing perceptions about the strength of confidence in one’s ability to quit smoking [34]. Response options range from 1 (not at all) to 7 (extremely), with higher scores representing a better outcome. An additional option, “Don’t know,” is also provided. Nicotine dependence will be assessed using the Fagerstrom Test for Nicotine Dependence scale, a six-item questionnaire measuring the quantity of cigarette consumption, the compulsion to use, and dependence [35].

Forgoing cigarettes will be assessed using daily logs submitted throughout the 4 weeks of the trial, with two items asking whether participants chose to skip cigarettes they normally would have smoked and whether they stubbed/butted out a cigarete before finishing it [34, 36]. Response options are as follows: 1 (no), 2 (yes, once), and 3 (yes, several times), with higher scores representing a better outcome. Quit intention will be measured with multiple items asking participants’ intention and motivation to quit in the next month and 6 months [37]. Response options range from 1 (not at all) to 7 (extremely), with higher scores indicating a strong intention to quit. An additional option, “Don’t know,” is also provided.

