**Outcomes**					
Cigarettes per day	x				x
Use of other tobacco products	x				x
Use of cessation medications	x				x
Forgoing cigarettes					x
Quit attempts	x	x	x	x	
Perceived risk of VLNCs	x	x	x	x	
Self-efficacy	x	x	x	x	
Quit intention	x	x	x	x	
Nicotine dependence	x	x	x	x	
Cigarette evaluation	x	x	x	x	
Carbon monoxide	x	x	x	x	

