For binary outcomes, such as making a quit attempt, we will be able to detect odds ratios (OR) between 1.27 and 1.41 for daily log data (28 observations per person, depending on the level of autocorrelations and missing data) and OR = 1.74–2.22 for weekly data (5 observations per person). Past research found baseline values of 35% for the proportion of participants who tried to quit using VLNCs [41]. We will be able to detect small effect sizes (small OR = 1.68, medium OR = 3.47, large OR = 6.71 [45]).

Overall, the study is sufficiently powered to detect small effect sizes, which is necessary based on past research that found that messaging campaigns have at most small effects [46, 47].

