## Data collection and management

### Plans for assessment and collection of outcomes {25a}

Data will be obtained via participant self-report surveys during in-person visits (collected using the REDCap system) and through daily logs (using the Twilio text messaging integration with REDCap), in addition to biochemical testing (expired CO for biochemical verification of smoking status) during in-person visits.

Standard operating procedures will be applied to each visit and procedure to ensure consistency. PI and Co-Is will train research staff and ensure quality control throughout the study, where the protocol and procedures will be carefully described. Case Report Form books will be created to maximize parallel recording of data across studies. Each visit will have a checklist of all the measures that need to be administered and the order in which these measures are administered. Additionally, online meetings will be held regularly with the lead site PIs and coordinators.

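### Quit attempts are scheduled and powered as an outcome but never defined in Outcomes {16}, and the power text gives them a daily-log odds ratio and a small-effect claim that do not apply

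*Protocol article*

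**What the plan says.** **Where quit attempts count as an outcome.** Objectives {10} promises effects on "cigarette dependence, and cessation-related outcomes over the study period". Table 2 has the row "Quit attempts" in its Outcomes block, marked at baseline, randomization and all four weekly visits, with no mark in the daily-log column. Section {15b} says: "At each weekly visit, participants will be asked if they have made a quit attempt in the past week". Sample size {19} speaks of weekly secondary outcomes related to cessation behaviors. Its binary paragraph opens "For binary outcomes, such as making a quit attempt, we will be able to detect odds ratios (OR", then gives 1.27 to 1.41 for daily logs and 1.74 to 2.22 for weekly data. It cites a 35% proportion who tried to quit, sets small at an odds ratio of 1.68, and concludes that small effects can be detected.

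**Where they are absent.** The primary and secondary outcome text under Outcomes {16} does not name them. The nearest item is intention: "Quit intention will be measured with multiple items asking participants’ intention and motivation to quit in the next month and 6 months". The hypotheses do not name them either, nor does the key secondary list in the administrative table ("Use of other tobacco products; Use of nicotine replacement therapy; Perceived risks of smoking VLNCs; Quit intention; Nicotine dependence; Forgoing cigarette behaviors").

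**The concern.** The section that defines outcomes and the sections that schedule and power them disagree on whether quit attempt is an outcome. Messages are meant to encourage quitting, and three of the four themes in the Messages section concern it. Yet the defined outcomes bearing on cessation are proxies: intention, self-efficacy, medication use and forgoing cigarettes. With no stated definition, time window or summary, a quit-attempt result from this open-label trial, which is already enrolling, could be built in several ways after data are seen and would be hard to defend as prespecified.

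The power text adds a second fault. A reader would take quit attempts to be powered at odds ratios as low as 1.27, or at least at a small effect. Neither follows from the article's own figures.

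**Working it through.** **1. Table 2 outcome rows against Outcomes {16}**

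| Table 2 row | Defined in {16}? |
|---|---|
| Cigarettes per day | yes (primary) |
| Other tobacco products | yes |
| Cessation medications | yes |
| Forgoing cigarettes | yes |
| **Quit attempts** | **no** |
| Perceived risk of VLNCs | yes |
| Self-efficacy | yes |
| Quit intention | yes |
| Nicotine dependence | yes |
| Cigarette evaluation | yes |
| Carbon monoxide | yes |

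Ten of 11 rows are defined.

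**2. Which odds ratio range can apply.** The daily-log column of Table 2 is marked for cigarettes per day, other tobacco, cessation medications and forgoing only. The Daily logs section describes tobacco use only. So 1.27–1.41 cannot apply to quit attempts, which leaves 1.74–2.22. Its lower end already exceeds 1.68.

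**3. Can the weekly range be reproduced?** Inputs from the article: 262 completers per group, so 131 per arm; 80% power; two-sided 0.05; control proportion 35%; 5 observations; up to 20% missing (131 × 0.8 ≈ 105 per arm). The autocorrelation ρ is not given, so I varied it from 0 to 1 as an assumption.

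- Effective number per arm = n × m / (1 + (m − 1)ρ).
- n = 131, m = 5, ρ = 0.5: 655 / 3 = 218. Detectable odds ratio 1.73, close to the stated 1.74.
- n = 105, m = 5, ρ = 1: 525 / 5 = 105. Detectable odds ratio 2.19, close to the stated 2.22 (power at 2.22 is 0.81).
- Over the whole span of ρ the detectable odds ratio runs from 1.37 (ρ = 0) to 2.02 (ρ = 1) with 131 per arm, and from 1.43 to 2.19 with 105.

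The stated range is therefore attainable with ρ from about 0.5 to 1, but cannot be confirmed exactly. With no missing data, 1.68 would come within reach only at ρ of about 0.42 or less (655 / 2.68 = 244 per arm, detectable 1.68). The article's own range excludes that.

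**4. One yes/no per participant.** Two-proportion test, pooled variance under the null:

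- p₂ = odds₂ / (1 + odds₂), with odds₂ = OR × 0.35 / 0.65.
- At OR 1.68: odds₂ = 0.905, p₂ = 0.475, difference 0.125.
- Null SE = √(2 × 0.4125 × 0.5875 / 131) = 0.0608. Alternative SE = √((0.2275 + 0.2494) / 131) = 0.0603.
- Power = Φ((0.12496 − 1.96 × 0.06083) / 0.06033) = Φ(0.095) = 0.54.

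| Per arm | Basis | Power at 1.68 | Detectable OR at 80% |
|---|---|---|---|
| 105 | completers, 20% missing | 45% | 2.19 |
| 131 | all completers | 54% | 2.02 (35% vs 52.1%) |
| 164 | all randomized (328 / 2) | 63% | 1.88 |

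An odds ratio of 1.68 needs 243 per arm for 80% power.

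**The case against.** **Quit attempts are treated as a secondary outcome if the article is read as a whole.** Table 2 lists them, {19} names weekly cessation behaviors as secondary outcomes, {27a} analyses secondary outcomes like the primary, and descriptive statistics are promised for all measurements. This stands. A reader might infer that the trial does not measure quitting, or would leave it unreported. The documents do not support that: attempts are asked about weekly, cigarettes are logged daily, and CO is taken at visits. What is missing is the definition.

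**The administrative list is headed as key.** It also omits self-efficacy, cigarette evaluation and CO, which {16} includes, so its silence proves little. Likewise, the hypotheses skip some outcomes that {16} defines. Both concessions stand; the point rests on {16} against Table 2 and {19}. The registry record is not at hand, so nothing is claimed about it.

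**Abstinence was never promised.** A reader might infer that a CO-verified abstinence endpoint is owed, because {25a} describes "expired CO for biochemical verification of smoking status". It is not. The objective speaks of cessation-related outcomes, and proxies qualify. A CO gate would also misclassify: other combusted products are permitted and may raise CO, and the 6 ppm figure is an entry criterion.

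**The power paragraph covers binary outcomes in general and does give the weekly range.** True, but it names quit attempt as its example, cites the quit-attempt proportion, and then claims small effects. For this outcome that claim contradicts its own figures.

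**Outcome detail is often left to a SAP or the full protocol.** That would excuse a thin definition. It does not explain why {16} describes ten of the scheduled outcomes and omits the one used to illustrate power.

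**Conclusion.** The point holds as an internal inconsistency with two parts. First, quit attempt is scheduled, collected and powered as an outcome, yet is the only one of 11 scheduled outcomes that {16} does not define. Second, the daily range of 1.27–1.41 does not apply to it, and the range that does, 1.74–2.22, misses the article's small effect of 1.68 throughout. Power at 1.68 for a per-participant analysis is about 54% (45% to 63% across the analysis sizes above).

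The power figures assume that 35% is the control proportion with any attempt over the study period, an unadjusted comparison within one of the three groups, and 1:1 allocation. The repeated-measures figures also assume a constant correlation, which the article does not state. The inconsistency in definitions rests on none of these. The primary outcome is unaffected.

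**What to change.** - **Outcomes {16}:** name quit attempt as a secondary outcome. One workable form is any attempt reported at post-randomization weekly visits 1–4 (yes/no per participant), compared by arm within each of the three groups by logistic regression with the primary-model covariates. Stating visits 1–4 matters because the report at the randomization visit precedes allocation. Align the hypotheses, or state that none is set for this outcome.
- **Sample size {19}:** limit 1.27–1.41 to binary outcomes that the daily log collects, such as any use of cessation medication. For quit attempts give only the weekly or per-participant detectable odds ratio (about 2.0 at 35% control with 131 per arm), and withdraw the small-effect claim for this outcome.
- **Optional:** report abstinence from cigarettes on the week-4 logs descriptively.

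**Cost:** wording, and one model in each of three groups, with no new data collection. The downside is one more secondary outcome with limited power, and a less favourable stated detectable effect. Data collection is expected to run to January 2029, so the definition can still be fixed well before the final analysis.

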**Protocol version {2}**

 October 2025. Version 4

## Introduction

### Background and rationale {9a}

Smoking remains the leading cause of preventable death and disease in the US [1, 2]. Tobacco-related health disparities endure, with smoking concentrated in socially and economically disadvantaged populations. Although most people who smoke in the US want to quit, only about 7% successfully quit each year [3], with even lower success rates among people with mental health conditions and those with low socioeconomic status (SES) [3–6].

To address this public health crisis, the FDA has issued a proposed rule to reduce nicotine in cigarettes and certain other combusted tobacco products (cigarette tobacco, roll-your-own tobacco, cigars, and pipe tobacco) to minimally addictive levels [7]. This groundbreaking strategy can potentially save millions of lives by increasing cessation rates and preventing people who experiment with cigarettes from developing an addiction and moving to regular smoking [8]. Many randomized clinical trials (RCTs) have found that very low nicotine cigarettes (VLNCs) are less addictive than regular cigarettes, reduce the number of cigarettes smoked per day, and increase quit attempts [9–11]. Studies with priority populations, including people with mental health conditions and those from low SES backgrounds, found that VLNCs reduce smoking behavior and nicotine dependence in these groups to a similar extent as in the general population, reinforcing the general applicability of the policy [12–18].

However, these RCTs evaluating the effects of smoking VLNCs did not incorporate messages about the VLNC products or the reduced nicotine policy; frequently, participants were blinded to the fact that they were smoking VLNCs. When the reduced nicotine policy is implemented in the real world, it will be publicized. Without appropriate educational messages, misinformation and misperceptions about the reduced nicotine cigarettes and the policy might proliferate, spurring backlash and ultimately reducing the potential effectiveness of the policy. Past studies documented various misperceptions about VLNCs, including the notion that they are less harmful than regular cigarettes [19–22], that they make people smoke more [23], appeal to people who formerly smoked, and are a conspiracy between the FDA and the tobacco companies to keep people hooked on nicotine via alternative delivery methods [24]. Therefore, implementing the reduced nicotine policy will require accompanying communication strategies that address misperceptions about VLNCs and the policy itself.

Messages correcting misperceptions around VLNCs may have a meaningful impact on perceived risk and behaviors. Past studies developed and tested the effects of messages on perceptions related to VLNCs and/or the policy, utilizing either textual statements or fully developed advertisements [25–30]. These studies suggest certain statements or ads can effectively reduce misperceptions. However, the messaging studies were mostly hypothetical, without participants actively using VLNCs. This study will take the next step by bringing together two previously separate areas of research: studies examining the behavioral effects of VLNCs use through RCTs, and those testing the effects of messages on correcting misperceptions about VLNCs in hypothetical scenarios. By assessing the effects of messages on people who smoke while they are using VLNCs, this study will provide important evidence to inform FDA regulatory actions around product review, product standards, and public education on nicotine.

